### Study design

The HeiLivCa trial is a prospective, multi-center, placebo-controlled, randomized, double-blind clinical trial with two parallel treatment groups receiving TACE plus sorafenib or TACE plus placebo. Patients in both groups will be treated with a maximum of four TACE procedures. For TACE carboplatin will be used as chemotherapeutic drug and lipiodol as embolizing agent. Four weeks after TACE, response will be evaluated by CT-imaging. Study medication will be stopped at progression. For patients without progression, treatment with sorafenib or placebo will be continued until LTx. All patients will be followed for 24 month after end of treatment. The duration of the overall trial is expected to last approximately 48 months. The actual duration of trial may vary due to the availability of patients meeting the criteria after registration for LTx. (Figure 1)

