### Study objectives

The primary objective is to evaluate the efficacy of TACE plus Sorafenib compared to TACE plus placebo in patients with HCC before LTx. The primary endpoint is the TTP based on radiological assessments, defined as the time from the date of randomization to disease progression. In the absence of a TTP event, TTP time will be censored at the date of last disease assessment. The secondary efficacy objectives are to assess the number or patients reaching LTx, disease control rates, 1- and 2-year OS after LTx, progression-free survival, number of TACE in each arm, quality of life, safety and toxicity.

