### Statistical considerations

Full analysis set will include all patients who are randomized, with study medication according to initial randomization, regardless of whether patients receive study medication or receive a different drug from that to which they were randomized. This population will be the primary population for evaluating the efficacy. Safety Population: The safety population consists of all patients who received at least one dose of study medication. This population will be the primary population for evaluating treatment administration/compliance and safety. TTP will be compared between arm A and arm B using the log-rank test (primary analysis). Median TTP with corresponding 95% confidence intervals (CI) will be estimated using Kaplan-Meier methods. The hazard ratio (arm B/arm A) will be estimated by proportional hazard regression. PFS and OS will be compared between arm A and arm B using a log-rank test stratified by the variables LTx (yes or no) and center. Median survival with corresponding 95% CIs will be estimated using Kaplan-Meier methods. The hazard ratio (arm B/arm A) will be estimated by proportional hazard regression with treatment and the factors used in the stratified log-rank test in the model. Estimates of the rates of patients reaching LTx in both arms, disease control rates, response rates, frequencies of TACE, overall survival, progression free survival and 95% confidence interval will be calculated for each treatment group. Response rates will be compared between treatment groups using the Cochran-Mantel-Haenszel test adjusting by the variable LTx (yes or no) and center. The health-related quality of life and disease/treatment-related symptoms scales will be scored according to the EORTC recommendations as described in the EORTC QLQ-C30 and QLQ-HCC18 scoring manual. Health-related quality of life subscales and single item subscores will be summarized by the mean and median for each arm and plotted by time. The change from baseline for all domains will be examined by treatment arm. All patient data (clinical and resource use) generated during the study will be recorded on the eCRFs specifically designed to meet the data recording requirements of the clinical study protocol. All data management activities will be done according to ICH-GCP guidelines. Responsibility for data management is the NCT. Throughout the study, all patient information in the eCRF will only be identifiable by means of an identification number (patient number) and patient initials.

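### PFS, OS and response are compared within LTx (yes or no) strata, although LTx follows randomization and is itself an efficacy outcome, so these secondary comparisons do not estimate the randomized effect

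*Protocol article*

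**What the plan says.** All three uses of LTx stand in the protocol article, Statistical considerations:

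- PFS and OS are compared between the arms "using a log-rank test stratified by the variables LTx (yes or no) and center".
- Their hazard ratios come from "proportional hazard regression with treatment and the factors used in the stratified log-rank test in the model".
- Response rates are compared with the "Cochran-Mantel-Haenszel test adjusting by the variable LTx (yes or no) and center".

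The primary TTP comparison in the same section is a log-rank test with no LTx stratum stated.

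Elsewhere the article treats LTx as something that happens during the trial. Under Study objectives, "The secondary efficacy objectives are to assess the number or patients reaching LTx". Under Study design, for patients without progression, "treatment with sorafenib or placebo will be continued until LTx". Statistical considerations also plans to estimate by arm the rate of patients who reach LTx, so one section uses LTx both as an outcome and as a stratum.

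**The concern.** A stratification factor has to be fixed before treatment can act on it. LTx is not. The article's own rationale is a chain: sorafenib delays progression, fewer patients leave the waiting list, more reach LTx, and those patients do well (Background gives about 70% survival at 5 years). Comparing the arms separately among transplanted and non-transplanted patients blocks that chain. A patient moved by the drug from the non-transplanted to the transplanted group counts as a change of stratum and not as a survival gain.

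The groups within a stratum are also no longer comparable as randomized. If the drug delays progression, each stratum holds a differently selected set of patients in each arm, and any prognostic factor that drives both progression and death becomes unbalanced. For response the order can run backwards, since LTx may follow from the response being tested.

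At stake are the tests and hazard ratios that would show whether delayed progression becomes patient benefit.

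**Working it through.** **1. Can LTx (yes or no) be a baseline factor?** The passages, side by side:

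- Table 1 excludes patients who are not eligible for LTx, so eligibility cannot define the two levels.
- Randomization and treatment describes 1:1 allocation and names no strata.
- Study design has study drug running up to LTx, so LTx comes after randomization.
- The Abstract says that progression leads to withdrawal from the waiting list, so LTx depends on progression.

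The factor is therefore the post-randomization event.

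**2. The plan's own figure.** Sample size calculation gives median TTP 4.5 and 7.5 months, so HR = 4.5/7.5 = 0.6. Schoenfeld events at one-sided 0.05 and power 0.875: 4 × (1.645 + 1.150)² / (ln 0.6)² = 31.25/0.261 ≈ 120, as stated. With 24 months of accrual and 9 of follow-up, the average event probability is 0.880 and 120/0.880 gives 136 patients, also as stated. These figures are not disputed. They supply the treatment effect used below. The article gives no power for PFS, OS or response.

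**3. How far treatment shifts the stratum.** Assume exponential times and LTx only if the organ comes before progression. Then P(LTx) = m/(m + w), with m the median TTP and w the median wait. The wait is an assumption.

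| Median wait (months) | Placebo | Sorafenib |
|---|---|---|
| 6 | 4.5/10.5 = 43% | 7.5/13.5 = 56% |
| 9 | 4.5/13.5 = 33% | 7.5/16.5 = 45% |
| 12 | 4.5/16.5 = 27% | 7.5/19.5 = 38% |

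Under the plan's own effect size the stratum differs between arms by 11 to 13 percentage points.

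**4. OS (simulation).** Assumptions, none in the documents: OS from randomization, median wait 6–12 months, median survival 9–16 months after progression and 120 months after LTx, 36 months of follow-up, 208 patients, and no drug effect other than delayed progression.

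| | Without LTx stratum | With LTx stratum |
|---|---|---|
| OS HR (A/B) | about 0.74–0.78 | about 0.86–0.96 |
| Power, one-sided 5% | about 35–55% | about 8–21% |

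Pairing the ends of the ranges on the log scale, the share of the effect that remains is ln 0.86/ln 0.74 = 0.151/0.301 = 50% at one end and ln 0.96/ln 0.78 = 0.041/0.248 = 16% at the other. In the plan's direction (B/A) the hazard ratio falls from about 1.28–1.35 to about 1.04–1.16.

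A second simulation used waits of 4–12 months, 9 or 16 months after progression, 70% survival at 5 years after LTx, pre-LTx liver death of 0.005 per month and censoring at 24–48 months. It gave 0.76–0.80 moving to 0.88–0.98, and power 0.28–0.47 falling to 0.06–0.16.

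**5. PFS (second simulation, with 15% recurrence over 5 years after LTx).**

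| Median wait (months) | HR without → with | Power without → with |
|---|---|---|
| 4 | 0.73–0.74 → 0.85 | 0.52–0.53 → 0.20–0.22 |
| 6 | 0.73 → 0.81 | 0.58–0.59 → 0.34–0.35 |
| 9 | 0.72 → 0.75 | 0.64–0.66 → 0.47–0.50 |
| 12 | 0.71–0.72 → 0.73 | 0.66–0.67 → 0.57–0.58 |

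**6. Response.** Assume response of 50% against 30%, 104 per arm, with LTx depending on response only. If 80% of responders and 30% of non-responders reach LTx, the expected LTx-yes counts (responders, non-responders) are 41.6 and 15.6 in arm A, 24.96 and 21.84 in arm B. The odds ratio there is (41.6 × 21.84)/(15.6 × 24.96) = 2.33, the same as the crude (0.5/0.5)/(0.3/0.7) = 2.33. The risk differences are 0.194 (LTx yes) and 0.113 (LTx no), with equal Mantel-Haenszel weights, so the pooled value is 0.15 against 0.20 crude. Expected Z falls from 2.94 to 2.57. With LTx in 90% and 10%, the risk difference is 0.08 and Z is 1.81.

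**7. Can stratifying create a signal?** Two cases, at 208 patients:

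- *No effect of any kind.* Arm is independent of LTx and outcome jointly. The stratified HR is 1.00, and rejection in favour of placebo is 4.4–5.4% at one-sided 5%.
- *Drug delays progression but not death, with an assumed prognostic frailty shared by both.* The stratified HR is 1.07. Rejection in favour of placebo rises from 2.1–2.5% to 5.6–6.4% across three runs at one-sided 2.5%, and from 4.5% to 10.8% in one run at one-sided 5%.

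**The case against.** **Only secondary analyses are touched.** This stands. The sample size, the interim look and the nominal levels rest on TTP, whose test carries no LTx stratum. The plan also reports LTx rates, OS and PFS by treatment group with 95% confidence intervals, and Kaplan-Meier medians, so the randomized contrast stays visible descriptively. Its test and hazard ratio do not.

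**The detail may be left to the SAP.** Assessment of quality of life does refer biometric detail to a SAP. But Statistical considerations has already named the stratum, so this is a stated choice and not an omission.

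**A reader might infer that a drug with no effect at all could look harmful.** The documents do not support this. Such a drug cannot shift the stratum, and step 7 shows no bias. The distortion needs a drug that acts on progression.

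**A reader might infer that the OS effect vanishes altogether.** That also goes too far. A stratified HR of 0.95 or more arises only at the edge of the assumed ranges, with short waits; with longer waits about half the log hazard ratio remains. The documents give neither the wait nor survival after progression, so no single figure can be claimed.

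**Immortal time in the transplanted stratum might be counted as a further bias.** It applies to both arms and distorts the comparison only through differential selection, which is already covered.

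**The OS definition is unsettled.** Study objectives lists 1- and 2-year OS after LTx, and the follow-up section times OS from end of treatment or LTx. The OS figures above therefore hold only if OS is counted from randomization. Counting it from LTx alone would not rescue the plan: every patient would be in the yes level, and the comparison would be limited to a group selected after randomization.

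**Conclusion.** The point holds for the secondary comparisons of PFS, OS and response. As written, they condition on an event that follows randomization, depends on progression and is itself an efficacy outcome, so they do not estimate the effect of randomized treatment.

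OS is hit hardest: under the assumptions in step 4, between about half and five-sixths of the log hazard ratio is lost, and power falls to about 8–21%. PFS loses less, clearly with short waits and little with long ones. For response the loss depends on how strongly LTx follows response; if LTx depends on response alone, the odds ratio is unchanged while the risk difference and test statistic shrink.

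The direction in these scenarios is attenuation, with possible apparent harm on OS if the drug delays progression but not death. All sizes are illustrations. The structural fault does not depend on them, and more patients or longer follow-up would not cure it. The primary TTP log-rank test stands.

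**What to change.** In Statistical considerations, before unblinding:

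- Delete LTx (yes or no) from the strata of the PFS and OS log-rank tests, from the PFS and OS proportional hazards models, and from the Cochran-Mantel-Haenszel test for response.
- Keep center, or other factors known at baseline, as the only stratification or adjustment factors.
- Continue to report LTx as an outcome by arm, as already planned.
- If the role of LTx is of interest, enter it as a time-dependent covariate in an analysis labelled supportive, and state that this is not the randomized comparison.

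The cost is one change of wording in the analysis section. It needs no further data, visits or patients and leaves the primary analysis and sample size as they are.

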
## Discussion

Tumor progress while waiting for LTx is common in HCC patients. Drop-out rates range between 30% to 50% [17]. The role of neo-adjuvant therapies during the time on the waiting list remains a matter of debate. Currently, TACE is the standard for bridging patients and has in addition shown good results for downstaging patients initially not eligible for LTx [18-20]. This information is based on case series, case-control studies, and cohort studies showing a 22–29% rate of complete necrosis for TACE [21-25]. Two studies employing TACE for bridging to LTx reported excellent outcome [7,8]. Nevertheless, recurrence rates were only low when applying the Milan criteria [4]. The impact of recent new treatment approaches; expanding transplant criteria and the availability of a systemic therapy with sorafenib on drop-out rate, recurrence and OS have to be assessed in randomized studies.

The HeiLivCa trial is an randomized, controlled, double-blind, multi-center trial attempting to maximize tumor growth control in patients with HCC awaiting LTx by adding sorafenib the most effective currently available systemic treatment to brdging with TACE, the current standard of care. Progression-free survival is the best surrogate endpoint in most solid malignancies, but it is a vulnerable endpoint in HCC since the underlying liver disease is a comorbidity with significant mortality that would potentially bias the evaluation of efficacy in this setting. According to the recommendation of a recent consensus conference of the AASLD and the EASLD, TTP is chosen as a more valid primary end-point. With regard to the potential side effects and possible cumulative adverse events in combination with TACE and LTx safety, efficacy and quality of life will be analyzed as secondary endpoints.

## Abbreviations

AASLD: American Association for Study of Liver Diseases; AFP: α-Fetoprotein; ALAT: Alanine Amino Transferase, also known as SGPT; ASAT: Aspartate Amino Transferase, also known as SGOT; BCLC: Barcelona-clinic liver cancer bid twice a day; BUN: blood urea nitrogen; CBC: complete blood count; CTC: Common Toxicity Criteria; EASLD: European Association for Study of Liver Diseases; Ecrf: electronic case report form; EMEA : European Medicines Agency; FDA: Food and Drug Agency; GGT : Gamma Glutamyl Transpeptidase; HBV: Hepatitis B virus; HCV: Hepatitis C virus; HCC: hepatocellular carcinoma; ICH-GCP: International Conference on Harmonization of Technical Requirements for Registration of Pharmaceuticals for Human Use – Good Clinical Practice; ISRCTN: International Standard Randomized Controlled Trial Number; LTx: liver transplantation; NCI: National Cancer Institute; NCT: National Center for Tumor Diseases; PT: Prothrombin Time; PTT: Partial Thromboplastin Time; PT/INR: Prothrombin time; TACE: transarterial chemoembolization; TTP: time-to-progression.
